**Intervention**

**Intervention and data collection**

The project will utilise a simple application (app)set up on each participant’s or parent/guardian’s mobile smartphone, tablet, or other device that will allow video capture and transmission of ICS inhaler administration. Before the study intervention period is initiated in a given subject, the participant and/or parents/guardians will be trained in use of the video DOT application and how to upload the videos to a web-based repository. As a general rule, it would be expected that young people greater than 12 years of age will record and upload the video themselves, while parent/guardian assistance will be needed for younger children. All mobile devices will be tested after installation to make sure the Dropbox®([https://www.**dropbox**.com](https://www.dropbox.com))repository connection is active and ready to use.

Usual asthma care for the participant will be adopted throughout the study. Regarding the inhaler use, children aged 5 years or older may administer the medication themselves while a parent/guardian will be responsible for inhaler administration in patients 2 up to 5 years of age. However, parent/guardian administration will be allowed if that is usual asthma care in any age child.

Patients who are enrolled in the study will be randomised into two groups (I-med or D-med) as previously described. Participants or parents/guardians of participants will be asked to capture a DOT video twice daily (morning and evening) on their mobile devices of ICS use by the patient. It will be requested that morning videos occur before 9am on school days and before 11am on weekends and holidays, and evening videos occur between the evening meal and bedtime. In the I-med group, participants will be asked to upload daily video recordings via the internet to a repository for a 6 week period at the start of the study. Participants in the D-med group will be free from DOT for the first 6 weeks of the study and will be asked to carry out their usual therapy management. After that, DOT as described above will be applied for the next 6 weeks.

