Researchers will evaluate the DOT uploads daily through their password protected access to the video repository. Children and their parent/guardians also will have access to their own videos within the password protected repository. A research team member will follow up with parents/guardians and/or a participant by telephone if two consecutive days of video uploads are missed. The asthma clinical team (consultant/nurse) providing the usual asthma clinical management will be notified about children identified with poor inhaler technique.

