**At study end (both groups)**

- GP prescribing records for the 12 months leading up to, and during the study time period
- Community pharmacy dispensing records for the 12 months leading up to, and during the study time period

Clinician assessment of participant asthma severity will be defined according to accepted guidelines and asthma control will be categorized as uncontrolled, partially controlled, or controlled (BMT/SIGN 2012). Data regarding the medication profile will include any respiratory or allergy drugs added or removed, existing drug dosage changes, and drugs initiated for respiratory infections.

Patient inhaler technique will be evaluated by reviewing each video from the first 2 days of the intervention period and then a sample (at least one weekly) of the videos that have been uploaded to the repository application. The presence/absence of every required video will be documented.

Inhaler technique will be assessed and categorized on a three-point scale as effective, partially effective or poor (Patterson *et al.*, 2005). Inhaler technique evaluation will be based on criteria relevant to the child’s inhaler manufacturer administration directions, such as removal of cover, priming of device, vigorous shaking before each actuation, respiratory expiration before actuation, and holding of breath after inspiration. Effective technique will be recorded when the participant meets all relevant criteria. Partially effective technique will be recorded when errors in technique are observed but it is thought that the participant would receive some medication. Poor inhaler technique will be recorded when critical errors in technique occur such that it is considered unlikely that any medication would be inhaled (Patterson *et al.*, 2005; Melani *et al.*, 2011).

Adherence will be calculated based on total number of videos submitted during the 6 week intervention divided by the number of days during which DOT monitoring has occurred.

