**Feedback questionnaires**

Parents/guardians will be asked to respond to feedback questionnaire to provide their views and experience about the use of the technology at the end of intervention (6 weeks) or in cases where a participant is unable to complete the study. Feedback questionnaires will be sent to each participant by the post and each participant will be contacted by telephone for a reminder if the questionnaire is not returned within a two week period. This feedback will be used to document participant’s experience or record any difficulties with using the mobile DOT approach in the study. Moreover, participants feedback will help us make improvements to the approach for the future. Two feedback questionnaires have been prepared by the research team: one for participants who completed the 6 week period of using mobile DOT (Appendix 20) and the second for participants who consented to take part but did not upload videos or who uploaded videos for a shorter period that the 6 weeks requested (Appendix 21).

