**Outcomes measure**

The primary outcome measures in this pilot study concern two areas. Firstly, the feasibility, practicality, and persistence of using a mobile DOT approach in the management of asthma in children and young people will be assessed by evaluation of ICS inhaler technique and monitoring inhaler use adherence. Secondly, asthma control associated with the mobile DOT approach will be assessed with clinical (including number of patients who progress to controlled category) and laboratory disease assessment, participant-reported medication adherence, and quality of life measurements (PAQOLQ/PACQOLQ and ACT/C-ACT).

Secondary outcome measures for the study include any impact of mobile DOT on participants’ inhaler technique and adherence. These two aspects of asthma management will be assessed by comparisons between intervention groups and within groups during, and across, phases of the study. Participant and parent/guardian factors that influence the impact of the DOT method on inhaler use and adherence also will be determined.

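### The video-based adherence measure mixes uptake of the filming technology with ICS-taking, and the same monitoring is used to judge feasibility

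*Protocol*

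**What the plan says.** The first primary outcome area is the feasibility, practicality and persistence of mobile DOT. The Outcomes measure section says that these "will be assessed by evaluation of ICS inhaler technique and monitoring inhaler use adherence". The same section lists the impact of DOT on technique and adherence as a secondary outcome.

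Under At study end (both groups), the formula begins "Adherence will be calculated based on total number of videos submitted during the 6 week intervention divided by the number of days", the days being those on which DOT monitoring took place. On missing recordings the section says only: "The presence/absence of every required video will be documented".

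Under Intervention and data collection, families are asked to "capture a DOT video twice daily (morning and evening") and, in the immediate group, to "upload daily video recordings via the internet to a repository for a 6 week period"; the delayed group does the same six weeks later. The device connection is tested after installation. The team makes contact "by telephone if two consecutive days of video uploads are missed".

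The Protocol has other sources as well. Objective 2 and the Data analysis section also draw adherence from MARS scores, GP prescribing records and dispensing records. The Feedback questionnaires section describes two postal forms about experience and difficulties, one of them covering "participants who consented to take part but did not upload videos" and families who stopped early.

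**The concern.** Objective 1 asks whether families can and will film inhaler use at home. Objective 2 asks whether children take their ICS. A missing video can mean that the dose was not taken, that it was taken but not filmed, or that it was filmed but the upload failed. The first concerns medicine-taking; the other two concern the technology. The formula treats all three alike.

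Two consequences follow. Adherence read from videos is biased downward by whatever share of taken doses is not captured. And if the video count feeds the planned regression on non-adherence, factors that predict poor filming will be mixed with factors that predict poor medicine-taking, which bears on objective 4.

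**Working it through.** **Inputs.** Two videos per day for 6 weeks (Intervention and data collection): 2 × 42 = 84 requested videos. The adherence formula is videos divided by days. The Protocol states no expected adherence or capture rate, so those below are assumptions.

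**Scale of the formula.** A child who submits every video scores 84 / 42 = 2.0, so the ratio is not a proportion. Dividing by 84 gives one.

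**What the count identifies.** Let *a* be the share of doses taken and *u* the share of taken doses that are filmed and uploaded. Expected videos = 84 × *a* × *u*.

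| *a* (assumed) | *u* (assumed) | Videos | Per day | Share of 84 |
|---|---|---|---|---|
| 1.0 | 0.5 | 42 | 1.00 | 50% |
| 0.5 | 1.0 | 42 | 1.00 | 50% |
| 0.9 | 1.0 | 75.6 | 1.80 | 90% |
| 0.9 | 0.8 | 60.5 | 1.44 | 72% |
| 0.9 | 0.6 | 45.4 | 1.08 | 54% |
| 0.9 | 0.5 | 37.8 | 0.90 | 45% |

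The first two rows are different children with the same score. The shortfall from true adherence is *a*(1 − *u*): at *a* = 0.9 it is 18, 36 and 45 percentage points for *u* = 0.8, 0.6 and 0.5.

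**Persistence and the denominator.** A family that films fully for 14 days and then stops has 28 videos. If monitoring days end with the last upload, the score is 28 / 14 = 2.0 and the lost persistence disappears. If they are the full six weeks, it is 28 / 42 = 0.67 and lost persistence is read as non-adherence.

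**Does the prompt call sort this out?** The trigger is "if two consecutive days of video uploads are missed", which has two readings. Suppose each video arrives independently with probability *p*, and *q* = 1 − *p*. The share of missing videos that fall in a qualifying run, away from the ends of the period, is:

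- Both videos absent on each day: *q*[1 − (1 − *q*²)²]. At *p* = 0.7, 0.3 × (1 − 0.91²) = 5.2%. At *p* = 0.5, 0.5 × (1 − 0.75²) = 21.9%. Allowing for the two end days gives about 5% and 21%.
- Any video absent on each day: 1 − *p*⁴. At *p* = 0.7, 1 − 0.49² = 76%. At *p* = 0.5, 1 − 0.25² = 94%. With end days, about 75% and 93%.

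Coverage therefore depends heavily on the reading, and on independence; gaps that cluster would be caught more often. On either reading, no outcome of the call is said to be recorded or to enter the adherence measure.

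**The other sources, side by side.** MARS is self-report. Prescribing and dispensing records show supply, not doses taken. The feedback forms come at the end of the period or when a family cannot complete. None is tied to a particular missing video, and the Protocol states no rule for combining or ranking them.

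**The case against.** The strongest reply is that video is not the only yardstick. MARS is completed at every visit, and GP and dispensing records cover the 12 months before the study as well as the study itself. None of these depends on filming, and a low video count alongside full dispensing and a high MARS score is informative. Feasibility also rests on inhaler technique and on the feedback forms, whose content is not shown, so nobody can say that they fail to ask why videos are missing. Ranking the adherence sources may be left to an analysis plan. Directly observed therapy also counts observed doses by design.

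Most of this stands, and it rules out the stronger readings. A reader might infer that objectives 1 and 2 cannot be separated, or that there is no way to tell poor filming from poor medicine-taking. The documents do not support that, because outside information exists. A reader might also infer that a child filmed only in the mornings would never prompt a call. That holds only if a missed day means both videos absent; on the other reading the call comes after two days. Nor does the Protocol make the video count the sole outcome of the regression.

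What remains is narrower. The one explicit formula counts an uncaptured dose as missed, and the other sources are not linked to it. An analysis plan could rank the sources, but it could not recover reasons that were never collected.

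**Conclusion.** The point holds in a limited form. Followed as written, the video measure understates adherence by the share of taken doses that are not captured, and the Outcomes measure section uses the same adherence monitoring to judge feasibility. That the count identifies only the product *a* × *u* needs no assumption beyond the formula. The size of the bias does: 18 to 45 percentage points under the assumed 90% of doses taken and 50% to 80% captured, and none if capture is complete. Any effect on the analysis of factors applies to the extent that non-adherence is defined from videos. The other sources reduce the problem without resolving it. This deserves correction before data collection because the missing information is cheap to record then and hard to reconstruct later.

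**What to change.** 1. **Outcomes measure:** define feasibility and persistence by the proportion of the 84 requested videos uploaded, the day of last upload, the number of prompt calls and the technical failures, alongside the feedback questionnaires.
2. **At study end (both groups):** label the video measure *video-confirmed doses, a lower bound on adherence*, with the 84 requested videos as denominator. The lower bound assumes that each counted video shows a dose actually taken.
3. **Existing prompt calls and the end-of-DOT visit** (week 6 immediate group, week 12 delayed group): record a reason for missing videos, coded as not taken, taken but not filmed, or filmed but upload failed.
4. **Reporting:** give adherence with and without the slots reported as taken, as a sensitivity bound. The two children with 42 videos would then read 50% to 100% and 50% to 50% if the families report accurately. Do not conclude non-adherence from the raw video count alone.

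The cost is wording in two sections and one field on contacts that already take place, with no extra visits. The drawback is that the reasons are family-reported, which is why they serve only as a bound. The video count still contributes to both constructs, but with its meaning stated for each.

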**Data analysis**

Statistical analyses will be conducted by the researcher after entering all data into SPSS (IBM SPSSv.23, USA). All nominal data collected during the study will be analysed using descriptive approaches. Group differences (I-med and D-med groups) will be studied using the independent sample Student t-test. If the data are not normally distributed non-parametric statistics will be utilised (Mann-Whitney U test for independent group differences). A paired Student t-test will be used to detect any differences associated with the study periods within each group

Adherence to ICS use in participants will be determined based on the patients’ general practitioner records of medicine prescribed and the patients’ records of medicine dispensed within the 6 week period, monitoring of video submissions, as well as the total scores achieved from the MARS questionnaires.

Categorical variables associated with non-adherence will be analysed using Chi-squared analysis. If the expected frequency falls below 5, the Fisher’s exact test will be employed.

Factors that affect the adherence to ICS inhaler use will be determined using patient demographic and clinical data together with responses obtained through administration of BMQ, CES-D, MARS, PACQOLQ/PAQOLOQ and ACT/C-ACT questionnaires to the participants and participants’ parents/guardians as appropriate. Multiple regression analysis will be performed to evaluate the relative contribution of different predictors to non-adherence.

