It is known that adherence to ICS in children is a complicated matter influenced by diverse issues including socioeconomic factors, parents’ beliefs about asthma and asthma medications, and poor patient-doctor communication (Osterberg and Blaschke, 2005; Armstrong *et al*., 2014). In addition, parent/guardian health issues such as depression or substance abuse may negatively affect adherence in young children as a result of the parent/guardian’s failure to remind, or assist the child in the use of their medication (Brackis-Cott *et al.*, 2003). Non-adherence to medication can have various negative patient consequences such as more frequent clinic visits, disease exacerbations, hospital admissions, and increased cost of care (AL-Jahdali *et al*., 2013).Indeed, a recent review of childhood asthma deaths in SE England showed that medication non-adherence was a contributing factor in more than 50% of cases, including patients with milder disease (Anagnostou *et al*., 2012)

Despite being an area of active research, many interventions such as isolated educational efforts are ineffective in improving adherence (Drotar and Bonner, 2009).In a qualitative study in the primary care setting, asthmatic children of parents who expressed medication beliefs of a high concern–low need pattern had poor outcomes. Researchers subsequently showed that these beliefs could be modified by repeated tailored education and close follow-up, to result in high medication adherence. They concluded that “it is not the education per se, but rather the intensity, quality and frequency of education about self-management and follow-up that help to improve adherence” (Klot *et al.*, 2011).A multicentre clinical trial in the USA was designed to determine what medication was best to add in children with severe asthma already taking ICS and LABA. Interestingly, the trial was cut short due to an inability to recruit an adequate number of children. Patient improvement while under close supervision during the run in period was the main reason for the lack of patient recruitment. (Strunk *et al.*, 2008)

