**(c) Sample size calculation**

The variability in quality of life (QOL) score changes in a similar population was reported in a pilot study to be 1.3 units (Young *et al.*, 2001). To have an 80% power to detect a statistically significant (P<0.05; two-tailed Student t-test) difference for effect of the intervention between groups of 1 QOL unit would require 36 children per group.

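### The effect of DOT is not tied to the week 0 to 6 comparison of I-med with D-med, the only randomised contrast of DOT with no DOT, and the paired and later tests are not ranked below it

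*Protocol*

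**What the plan says.** The protocol's Study design section gives I-med the intervention in weeks 0 to 6, with follow-up visits at weeks 12 and 18. For the other arm, Intervention and data collection states: "Participants in the D-med group will be free from DOT for the first 6 weeks of the study". D-med then has DOT in weeks 6 to 12 and follow-up at weeks 18 and 24.

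The Data analysis section plans an independent-samples t-test (or Mann-Whitney U test) between I-med and D-med, with no time point or period attached. It continues: "A paired Student t-test will be used to detect any differences associated with the study periods within each group". It does not say which of these tests answers the question of effect.

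Under Outcomes measure, the secondary outcomes are the impact of mobile DOT on inhaler technique and adherence, to be judged by "comparisons between intervention groups and within groups during, and across, phases of the study". Adherence sources listed in Data analysis include prescribing records, "records of medicine dispensed within the 6 week period, monitoring of video submissions" and MARS scores.

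The Sample size calculation rests on a difference between groups in QOL score.

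**The concern.** The delayed-start design gives one clean estimate of what DOT adds: the difference between the arms in change from week 0 to week 6. After that D-med also receives DOT and the no-DOT comparator is gone.

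A paired test within I-med measures DOT plus everything else that moves the score over the same weeks. Recruitment requires partially controlled or uncontrolled asthma, so some regression to the mean is plausible. Usual clinic care continues, and medication changes are expected to the extent that they are recorded at every visit. A significant paired result therefore does not separate DOT from these influences.

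The later group comparisons have a different weakness. At week 12 the contrast is DOT just finished (D-med) against DOT finished six weeks earlier (I-med). At week 18 both arms are in follow-up. These contrasts inform durability and do not measure DOT against no DOT.

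With no ranking in the text, a report could rest a claim of benefit on two significant pre-post tests when DOT does nothing. It could also read a null week-12 difference as failure when DOT works and lasts.

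**Working it through.** **Inputs.** From Sample size calculation: variability of QOL change "reported in a pilot study to be 1.3 units", read here as an SD; "P<0.05; two-tailed Student t-test"; "To have an 80% power to detect a statistically significant"; a difference of 1 unit; 36 per group. Assumed, because the documents give no figure: the mean improvement without DOT, and the share of the DOT effect that persists in I-med from week 6 to week 12.

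**The plan's own figure.** n per group = 2 × (z for 0.975 + z for power)² × SD² / difference².
- 80% power: 2 × (1.960 + 0.842)² × 1.69 / 1 = 26.5, so 27 (28 with the exact t-test).
- 90% power: 2 × (1.960 + 1.282)² × 1.69 / 1 = 35.5, so 36 (37 with the exact t-test).

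The stated 36 therefore does not follow from 80% power. It gives about 90% power for 1 unit (0.896 with the t-test). That is a separate matter and does not weaken the present point. It means that the week 0 to 6 contrast is well powered on the plan's assumptions.

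**Paired test with no DOT effect.** SE = 1.3 / √36 = 0.217. The critical t on 35 degrees of freedom is 2.030, so a mean change of 2.030 × 0.217 = 0.44 units is significant. The noncentrality is drift / 0.217.

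| Assumed drift (units) | Noncentrality | Paired test significant |
|---|---|---|
| 0.25 | 1.15 | 20% |
| 0.50 | 2.31 | 61% |
| 0.65 | 3.00 | 83% |

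A drift common to both arms cancels in the group comparison of week 0 to 6 change, so that test stays at 5%.

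**Simulation of selection on a low baseline.** Assumptions: enrolment of the lowest half or lowest third, test-retest correlation 0.5 to 0.8, SD of change 1.3 before selection, 36 per group, no DOT effect. The mean change is +0.33 to +0.72 units. The paired test is significant in 35% to 94% of trials. The group test of the same change rejects in about 4% to 5%.

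**Week-12 group comparison.** Let the effect of DOT be 1 unit at the end of DOT in each arm, and let a share c persist in I-med six weeks later. The expected I-med minus D-med difference is −(1 − c). Its SE is 1.3 × √(2/36) = 0.306.

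| Share persisting, c | Expected difference | Test significant |
|---|---|---|
| 0 | −1.0 | 90% |
| 0.5 | −0.5 | 36% |
| 1 | 0 | 5% |

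An effective and lasting intervention gives no difference. One that fades completely gives a difference favouring D-med.

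**Adherence measures.** Video adherence is defined under Outcome measurements only for the six-week intervention, so D-med has none in weeks 0 to 6. MARS is collected in both arms at weeks 0 and 6. Prescribing and dispensing records cover the whole study, and inhaler technique is listed at each clinic visit. Comparators for weeks 0 to 6 therefore exist in both arms.

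**The case against.** The trial is sized on a difference between groups, the group test is listed first in Data analysis, and D-med is DOT-free until week 6. A reader could fairly take week 0 to 6 as the intended contrast and leave the time point to a statistical analysis plan. The paired test is described only as detecting differences associated with study periods, which is not a causal claim. D-med's own weeks 0 to 6 would reveal drift. Later visits are labelled follow-up, persistence is a stated objective, and the study is called a pilot.

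Much of this stands, and it limits the point. A reader might infer several stronger things that the protocol does not support:
- That the groups will be tested for effect at every phase on all outcomes. Data analysis is silent on timing, and the wording about phases covers only technique and adherence.
- That the later group contrasts are non-randomised. The arms remain as randomised; the contrast is simply no longer DOT against no DOT.
- That video adherence will be tested between groups. No section specifies this.
- That the Background proves improvement without DOT. It says of an earlier trial: "Patient improvement while under close supervision during the run in period was the main reason for the lack of patient recruitment". DOT is itself a form of supervision, so this is not clean evidence of drift or of regression to the mean.

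The objection does not remove the point. For technique and adherence, the protocol names comparisons within groups and across phases as the way to assess the impact of DOT. An unspecified time point can be left to an analysis plan, but that stated route to an effect claim would have to be overridden. Nothing in the text uses D-med's lead-in period as a control for the paired tests.

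**Conclusion.** The point holds as one of anchoring and ranking, and should be fixed. A valid randomised comparison is available and its data are collected, but the protocol does not name it as the estimate of effect or place the paired and later tests below it. The size, 20% to 83% significant paired tests with no DOT effect, rests on an assumed drift of 0.25 to 0.65 units, an SD of change of 1.3 and 36 children with complete data. The documents do not show that such drift will occur. They show only that the recruited population and continuing care make it plausible. It would go too far to say that the trial's aim will necessarily be answered by non-randomised comparisons, since the sizing already points to the group difference.

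**What to change.** In Outcomes measure and Data analysis:

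1. State that the effect of DOT is the I-med minus D-med difference in change from week 0 to week 6, preferably adjusted for the baseline value. This agrees with the between-group sizing.
2. Label the paired within-group tests and the week 12 and week 18 group comparisons as supportive or descriptive (durability, replication in D-med), with no claim of efficacy from them.
3. For adherence between groups, use MARS at week 6 and the prescribing and dispensing records over weeks 0 to 6. For technique, use the clinic-visit assessment at week 6.
4. Use video adherence only to describe uptake.

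The cost is wording alone: no added visit, measurement or participant. On the plan's own assumptions the week 0 to 6 test keeps about 90% power for 1 QOL unit at 36 per group.
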